## Abstract

**Background:**

Whilst multi-parametric magnetic resonance imaging (mp-MRI) has been a significant advance in the diagnosis of prostate cancer, scanning all patients with elevated prostate specific antigen (PSA) levels is considered too costly for widespread National Health Service (NHS) use, as the predictive value of PSA levels for significant disease is poor. Despite the fact that novel blood and urine tests are available which may predict aggressive disease better than PSA, they are not routinely employed due to a lack of clinical validity studies.

Furthermore approximately 40 % of mp-MRI studies are reported as indeterminate, which can lead to repeat examinations or unnecessary biopsy with associated patient anxiety, discomfort, risk and additional costs.

**Methods/Design:**

We aim to clinically validate a panel of minimally invasive promising blood and urine biomarkers, to better select patients that will benefit from a multiparametric prostate MRI. We will then test whether the performance of the mp-MRI can be improved by the addition of an advanced diffusion-weighted MRI technique, which uses a biophysical model to characterise tissue microstructure called VERDICT; Vascular and Extracellular Restricted Diffusion for Cytometry in Tumours.

INNOVATE is a prospective single centre cohort study in 365 patients. mp-MRI will act as the reference standard for the biomarker panel. A clinical outcome based reference standard based on biopsy, mp-MRI and follow-up will be used for VERDICT MRI.

**Discussion:**

We expect the combined effect of biomarkers and VERDICT MRI will improve care by better detecting aggressive prostate cancer early and make mp-MRI before biopsy economically viable for universal NHS adoption.

**Trial registration:**

INNOVATE is registered on ClinicalTrials.gov, with reference NCT02689271.

**Electronic supplementary material:**

The online version of this article (doi:10.1186/s12885-016-2856-2) contains supplementary material, which is available to authorized users.

## Background

The management of prostate cancer poses difficult challenges, which is largely because we lack the necessary tools to predict its presence, and discern between indolent disease with a small chance of clinical manifestation and aggressive tumours that are more likely to be lethal. Since prostate cancer is a complex disease, it is unlikely to be fully characterised with a single fluidic or diagnostic imaging marker.

### The standard and our institutional diagnostic pathways

After presenting with symptoms, or requesting screening for prostate cancer, patients typically undergo a digital rectal exam (DRE), combined with a prostate-specific antigen (PSA) blood test.

### PSA

PSA is a glycoprotein enzyme produced by normal prostate epithelium and is routinely used as a serum biomarker for prostate cancer, with raised levels typically provoking trans rectal ultrasound (TRUS) biopsy. However, in addition to prostate cancer, raised PSA levels are encountered in benign prostatic hyperplasia (BPH), prostatitis and normal prostate tissue, the PSA test has a fairly flat receiver operator characteristic curve, resulting in false positive and negative results meaning it is relatively poor at predicting or excluding significant prostate cancer [1, 2], which drives the need for more specific circulating biomarkers in its diagnosis. Circulating biomarkers in serum, plasma, urine, and prostatic fluid have all been explored, but thus far remain invalidated to a defined standard in a cohort collected under standardised conditions.

### PCA3

PCA3 (prostate cancer antigen 3) is the only other routinely available biomarker, it is currently only available in a private healthcare setting. The PCA3 test is carried on urine out after DRE and detects a prostate specific non-coding ribonucleic acid (RNA). The test has shown clinical utility in diagnosing prostate cancer and can discriminate tumour cells from benign [3–5]. When used alongside magnetic resonance imaging (MRI) it shows a correlation with tumour volume but PCA3 does not appear to correlate with other clinical parameters such as stage and grade [6]. When used alongside MRI the accuracy of the PCA3 test can be improved, PCA3 score has also been shown to correlate with suspicious MRI findings and therefore could be used to select patients that require an MRI, or because MRI outperforms the PCA3 it may have greater utility in stratifying patients for active surveillance or further biopsy [7–9].

### MRI

In the last 5 years, the prostate cancer community has undergone a pivotal change away from random transrectal ultrasound (TRUS) sampling of the prostate and towards image guided biopsy requiring multiparametric (mp)-MRI, including T2 weighted (T2W), diffusion weighted (DWI) and often dynamic contrast enhanced (DCE) imaging.

In January 2014 the National Institute of Clinical Excellence (NICE) issued revised guidelines on the management of prostate cancer, which included the use of mp-MRI in prostate cancer diagnostics [10]. In this document, MRI was only recommended in those with a negative TRUS and for staging where a change in tumour (T) or nodal (N) staging would alter management. The reason for this is likely to be due to the fact that mp-MRI remains a less than perfect test. For example, mp-MRI is relatively expensive, approximately 40 % of patients have equivocal findings and performance is modest for detection of small volume (<0.5 cc) tumour, lower grade aggressive disease (secondary Gleason pattern 4) and for lesions within the transition zone. In addition, the correlation of mp-MRI derived quantitative metrics with Gleason grade is only moderate; meaning it lacks biological specificity. This means further repeat multiparametric MRI studies or unnecessary biopsies are often necessitated, with associated patient discomfort, additional risks and costs.

## Our proposed new pathway

To address these limitations, we propose an approach integrating promising fluidic markers together with advanced diffusion weighted MRI (VERDICT: Vascular, Extracellular and Restricted DIffusion for Cytometry in Tumours) within the diagnostic paradigm (Fig. 1).

**Fig. 1 Fig1:**
[figure not shown]
Standard, our institutional and proposed new pathways for prostate cancer diagnosis

### Novel serum and urine biomarkers

The fluidic biomarkers we propose to investigate in our study have been selected based on the number of studies, patient reports and the ability of a marker to discriminate tumour from benign or predict poor outcome (Additional file 1). All markers can be tested in minimally invasive samples e.g. whole blood, serum, plasma or urine. We envision that these markers would help select patients most likely to benefit from subsequent mp-MRI, thereby rationalising valuable NHS resources. Horizon scanning will continue throughout the study to include any new and promising markers.

### VERDICT MRI

Most diffusion-weighted MRI studies have used the technique in its simplest form by calculating the apparent diffusion coefficient (ADC) to identify clinically significant tumor foci more clearly [11, 12]. In general, ADC values are lower in prostate carcinoma compared with healthy tissue but ADC values in both tissue types vary widely and overlap substantially [12–14].

The recent VERDICT MRI technique [15] offers the potential for explicit characterisation of tissue histology non-invasively. A proof-of-concept study for assessment of human prostate cancer [16] provided the basis for a first-in-man study of clinical validity. In this study, we imaged 8 patients with histologically confirmed peripheral zone cancer and demonstrated significant elevation in tumour fractional intracellular and fractional vascular volume, and a reduction in fractional extracellular extravascular volume, in keeping with disease histology.

Since this work, the MRI protocol has been optimised, using a computational optimisation framework [17] to reduce the VERDICT scan time from 40 min to a more clinically acceptable time of 15 min.

This is the world’s first clinical trial to investigate the use of VERDICT MRI. We envision that application of VERDICT MRI will improve the specificity of mp-MRI, reduce the number of indeterminate examination results and provide evaluation of the specific histological feature changes associated with cancer.

## Methods and analysis

### Design

INNOVATE is a prospective cohort study with single centre recruitment. The primary objective is to assess whether supplementary VERDICT MRI improves the diagnostic accuracy of mp-MRI for detection of significant prostate cancer by a minimum of 10 %. The definitions of significant cancer have been provided previously [18].

Participants undergo standard mp-MRI [19] ± biopsy, together with studied index tests (fluidic markers and VERDICT MRI). A 50 patient pilot phase held over 1 year will provide histologically validated VERDICT MRI studies in order to familiarise radiologists and ascend the learning curve necessary for clinically interpreting VERDICT images. Initial evaluation of fluidic biomarker performance for prediction of a negative mp-MRI result will be conducted at the end of year 1 to derive thresholds for prospective application. An evaluation phase held over 2 years will prospectively test the added diagnostic accuracy of VERDICT to standard mp-MRI. During the evaluation phase, selected fluidic biomarker thresholds will be applied to collected samples to prospectively categorise patients into those expected to achieve negative and positive (with a lesion) mp-MRI scores.

### Patient population

Inclusion, exclusion and withdrawal criteria are provided in Table 1 below.

**Table 1 Tab1:** Inclusion, exclusion and withdrawal criteria

Patient Inclusion Criteria
1. Men referred to our center for prostate mp-MRI following biopsy elsewhere
2. Biopsy naive men presenting to our institution with a clinical suspicion of prostate cancer
Patient Exclusion Criteria
1. Men unable to have a MRI scan, or in whom artifact would reduce quality of MRI
2. Men unable to given informed consent
3. Previous treatment (prostatectomy, radiotherapy, brachytherapy) of prostate cancer
4. On-going hormonal treatment for prostate cancer
5. Previous biopsy within 6 months of scheduled mp-MRI
Withdrawal criteria
1. Images inadequate for analysis due to artifact or image acquisition problems even after a repeat scan

### Informed consent

Informed consent is a prerequisite and will be carried out on the day of the trial interventions, following a minimum 24-h period of consideration to participate in the study.

### Trial Interventions

#### The index test – VERDICT MRI

All studies will be performed on a 3 T MRI scanner (Achieva, Philips, Amsterdam, NL). The total MRI protocol including routine mp-MRI will be limited to a maximum of 1-h scan time inclusive of 15 additional minutes allowed for VERDICT MRI. The mp-MRI protocol will be standardized, as recommended as per the UK consensus guidelines on prostate MRI [19], Table 2 below. 20 patients with tumours will undergo repeat studies, with one group having immediate repeatability (back to back scans) and another undergoing repeat studies within a week to gauge the short term repeatability of the parametric maps generated by VERDICT.

**Table 2 Tab2:** MRI phasing details for standard multiparametric prostate MRI

Sequence	Coil	TR	TE	FA degrees	WFS(pix)	BW Hz/Px	Fov mm	Slice thickness mm	Gap	TSE factor	Phasing direction	FS	ACQ matrix	TFE shots	TFE shot interval (ms)	Total scan duration
T2 TSE coronal	Dual	6128	100	90	2.704	160.7	180	3	3	16	R > L	No	300 x 290			05:55.4
T2 TSE axial	Dual	5407	100	90	2.704	160.7	180	3	0	16	R > L	No	300 x 290			05:13.6
T2 sag REF	Dual	1579	100	90	1.999	217.3	240	5	5	20	A > P	No	120 x 89			00:18.9
T1W TSE	Dual	487	8	90	1.997	217.6	240	3	3	4	R > L	No	184 x 184			03:06.8
DWI 0 150 500 1000	Dual	2753	80	90	40.353	10.8	220	5	0		A > P	SPAIR	168 x 169			05:16.5
DWI b2000	Dual	2000	78	90	44.108	9.9	220	5	0		A > P	SPIR	168 x 169			03:40.0
DCE 2 dyn mod SENSE	Dual	5.8	2.8	90	1.766	246.1	180	3	0	38 (TFE)	R > L	SPAIR	140 x 177	49	280	00:28.9
DCE 20 dyn mod SENSE	Dual	5.8	2.8	90	1.766	246.1	180	3	0		R > L	SPAIR	140 x 162	45	280	04:14.1

This is supplemented by an optimised VERDICT MRI technique based on previously reported work [15], which uses a Pulse-gradient spin-echo sequence and a 32 channel cardiac coil with *b* values of 90-3000 s/mm^2^ in 3 orthogonal directions. For *b* < 500 the number of averages (NAV) = 6, for 500 < *b* < 1000 NAV = 12 and for *b* > 1000 NAV = 18 with voxel size = 1.3 × 1.3 × 5 mm, matrix size = 176 × 176. The data is normalized with a *b* = 0 image for every echo time (TE) to avoid T2 dependence. Scanning parameters for VERDICT MRI are provided in Table 3.

**Table 3 Tab3:** VERDICT MRI diffusion gradient parameters

*b* value s/mm^2^	∆/δ ms	TE ms	|G| T/m
3000	19.7/38.8	80	0.0579
2000	13.2/32.3	67	0.0758
1500	24.7/43.8	90	0.0311
500	12.2/31.3	65	0.0415
90	4.7/23.8	50	0.0506

The parametric maps generated from the VERDICT scans produce measurements of the intracellular volume fraction (fIC), cell radius (R), cellularity, extravascular extracellular volume fraction (fEES) and vascular volume fraction (fVasc). We also retain the fitting chi-squared objective function (fobj), which is a sum of square differences adjusted to account for offset Rician noise bias, as in [15, 16], to confirm successful fitting of the biophysical VERDICT model has been or highlight regions where the model is not appropriate. A typical example of such parameter maps is provided in Fig. 2.

**Fig. 2 Fig2:**
[figure not shown]
VERDICT parameter maps. Images have been colour scaled. L to R, top to bottom: Original image b = 0 diffusion-weighted image. Prostate + lesion showing original image with superimposed segmented lesion. Prostate segmentation + lesion segmentation. fIC = intracellular volume fraction. R = cell radius. Cellularity map = calculated parametric map which shows the measured number of cells per voxel. fEES = Extracellular, extravascular volume fraction, fVASC = vascular volume fraction. fobj = objective function. fIC, fEES and fVASC are all fractions, which add to 1. Cellularity is number of cells per voxel, with units of cells/μm3. Objective function highlighting the ‘goodness of fit’ for the VERDICT model

#### Reporting of mp-MRI and VERDICT MRI

MRI examination reports should record the suspicion of cancer using an ordinal Likert scale (1 to 5): 1- tumour highly unlikely, 2- tumour unlikely, 3- equivocal, 4- tumour likely and 5- tumour highly likely. Strong evidence from multiple institutions confirms mp-MRI is able to accurately detect and localise ≥0.5 cc prostate cancer ≥ Gleason 4 [19–21].

The first 50 patients VERDICT MRI studies will be used to familiarise radiologists with VERDICT MRI derived parameter maps, as they ascend the learning curve. Radiologists will be allowed to review the VERDICT MRI with access to biopsy results for correlation once available. Potential conclusions drawn from VERDICT datasets will not be included in clinical MRI reports as at this stage we will not know the sensitivity or specificity of VERDICT. These patients will not form part of the main trial cohort.

A locked sequential read report for mp-MRI prior to and following evaluation of VERDICT MRI will be performed for the main trial cohort. mp-MRI results will be made available to the clinical team as per standard practice. VERDICT MRI results will be collected using a case report form but will not be revealed to the clinical care team so as not to negatively influence patient care. A radiologist will compare in vivo MR images and note areas of abnormality as defined by the conventional mp-MRI, and corresponding regions of interest (ROIs) on the parametric VERDICT maps. In the case of prostatectomy specimens, MR slices will be visually registered to the pathological specimen. For biopsies targeted using MRI, the lesion location can be ascertained from the operation note/pathology report and in the case of positive cores, specimens can be considered to be a successful target.

Quantitative measurements of vascular volume fraction, extracellular extravascular volume fraction, intracellular volume fraction, cell radius and cell density will be derived from VERDICT for correlation against histological measures (see section 3.4.3).

#### Fluidic markers from blood and urine

Whole blood, serum, plasma and urine will be collected from all patients in the study using existing standard operating procedures (SOPs) and assayed for diagnostic markers (PCA3, AGR2 (Anterior gradient protein 2 homolog), SPON2 (spondin 2), TMPRSS2 (Transmembrane protease serine 2), EN2(Homeobox protein engrailed-2), MSMB(Beta-microseminoprotein), GDF15(Growth differentiation factor 15), SIK2 (Serine/threonine-protein kinase) and CD10(cluster of differentiation 10)). Protein markers in all matrices will be assayed on a MesoScale discovery (MSD) platform and deoxyribonucleic acid (DNA) will be extracted from whole blood to investigate 22 prognostic single nucleotide polymorphisms (SNPs) associated with aggressive disease. RNA for the PCA3 and TMPRSS2 quantification from urine will be extracted according to an SOP already developed in our laboratory. qPCR for PCA3, TMPRSS2, 3 control genes (TBP (TATA binding protein), SDH (succinate dehydrogenase), RPLP2 (60S acidic ribosomal protein P)) and PSA will be used in triplicate to quantify gene expression. During the pilot phase we will continue to horizon scan for new markers and have included scope to add 2 further markers as evidence comes to light and assays are developed e.g. GOLM1 (golgi membrane protein 1), NAALADL2 (N-Acetylated Alpha-Linked Acidic Dipeptidase-Like 2).

We will also extract exosomes from the serum and plasma (when possible) of patients to derive molecular tumour characteristics using fluorescence-lifetime imaging microscopy (FLIM) based measurements as well as analysis of exosomal micro RNA (miRNA) that are known to be associated with cell-to-cell communication and the development of cancer as well as immunosuppression leading to the development of further pre-metastatic niche. Functional blood-derived miRNAs have been recognised as potential robust biomarkers in the detection of various types of cancer. The ability to screen for these miRNAs and to perform FLIM of the epidermal growth factor receptor (ErbB) family members will add important prognostic and predictive information for diagnosis and stratification of patients to treatment. Finally, we will separate peripheral blood mononuclear cells (PBMCs) from whole blood of newly diagnosed prostate cancer patients to perform immunophenotyping of immune cell populations with an ultimate goal to provide multi-modality patient stratification.

### Defining reference standards

#### Biomarker panel: mp-MRI result

Since it is envisaged that diagnostic biomarker thresholds in the blood or urine will be able to predict a negative mp-MRI result, and act as a gatekeeper to effectively rationalise its use, conventional mp-MRI result will form the reference standard. Any lesion (Likert score 3 and above) will be considered to be a positive result. VERDICT MRI will not be considered as part of the reference standard for fluidic markers as the utility of VERDICT MRI remains unknown.

### VERDICT MRI: histology/mpMRI based reference standard

A lesion based reference standard will be derived (Fig. 3). mp-MRI has a 90-95 % negative predictive value for exclusion of aggressive disease [22] and will therefore form the reference for the index tests when mp-MRI is negative (Likert score 1-2/5). The positive predictive value of mp-MRI is limited and reported between 60-70 %. Therefore, where mp-MRI is positive (Likert score 3-5/5) a prostatectomy or biopsy will be performed if clinically appropriate. The prostatectomy or biopsy will then supersede the mp-MRI as the reference standard. Where a biopsy or prostatectomy is not performed, patients will be followed up with interval (6 months-1 year) mp-MRI as part of standard clinical care. A progressive Likert score (3/5 - > 4/5 or 5/5) or a progressive lesion (previously scored 4-5) on repeat mp-MRI will be considered as positive for the reference standard. A negative Likert score (1-2/5) on the repeat mp-MRI will be considered as negative for the reference standard. Lesions that remain stable with Likert score 3/5 will be deemed indeterminate and excluded from analysis unless biopsied. Based on previous internal audit, the total number of excluded patients is predicted to be approximately 10 %.

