### Statistical considerations

#### Sample size calculation

A sample size of 280 subjects achieves 80 % power to detect a difference of 0.1 between two diagnostic tests whose specificities are 0.7 and 0.6. This calculation uses a two-sided McNemar test with a significance level of 0.05. The prevalence of patients with no cancer or insignificant cancer (≤Gleason 3 + 3) is estimated at 0.6. The proportion of discordant pairs is estimated at 0.2. Allowing for 10 % of patients being excluded from the reference standard, a total of 365 patients (50 to allow radiologist training, followed by 315 patients for the main study) will be recruited. Based on current practice at our institution, approximately 10 mp-MRI studies are performed per week in men that meet the eligibility criteria. With a 50 % recruitment rate (note our audit data from previous similar studies supports a recruitment rate of 90 %), complete recruitment is expected to take 73 weeks.

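### Unbiopsied lesions that progress on repeat mp-MRI are labelled reference-positive without histology, so the comparator decides part of its own reference standard

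*Protocol article*

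**What the plan says.** The section on the VERDICT reference standard (protocol article, heading VERDICT MRI: histology/mpMRI based reference standard) starts from the performance of mp-MRI. It states "The positive predictive value of mp-MRI is limited and reported between 60-70" per cent and, for that reason, calls for biopsy or prostatectomy of Likert 3-5 lesions where clinically appropriate. Histology then replaces mp-MRI as the reference.

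Without tissue, a repeat mp-MRI at 6 months to 1 year decides:
- Likert 3 rising to 4 or 5 is positive. So is the second case: "a progressive lesion (previously scored 4-5) on repeat mp-MRI will be considered as positive for the reference standard".
- Likert 1-2 on the repeat scan is negative.
- For the stable equivocal lesion: "Lesions that remain stable with Likert score 3/5 will be deemed indeterminate and excluded from analysis unless biopsied".

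The target condition is significant prostate cancer (Design; Table 5). The sample size section puts men with Gleason 3+3 or less on the negative side: "The prevalence of patients with no cancer or insignificant cancer (≤Gleason 3 + 3) is estimated at 0.6". The analysis compares lesion-based specificity of mp-MRI with and without VERDICT at a Likert threshold of 3 (Data analysis and outcome assessment, VERDICT MRI).

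**The concern.** The paragraph finds one positive mp-MRI insufficient and asks for tissue. It then lets a further mp-MRI reading stand as proof of significant cancer when tissue is absent. Progression on imaging does not supply a Gleason score, and the Background section on MRI itself says that mp-MRI metrics correlate only moderately with grade and lack biological specificity. mp-MRI is also the comparator in the primary analysis, so its own follow-up fixes some of the labels against which it is judged.

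What is at stake is the specificity gain. A benign or Gleason 3+3 lesion scored 3 or more is an mp-MRI false positive, which is where VERDICT is meant to help. If it progresses on imaging and is never sampled, it moves to the positive side of the reference standard and drops out of the specificity denominator. A correct VERDICT downgrade of it then earns nothing.

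**Working it through.** **Inputs** (Sample size calculation): "A sample size of 280 subjects achieves 80 % power to detect a difference of 0.1"; "two diagnostic tests whose specificities are 0.7 and 0.6"; "This calculation uses a two-sided McNemar test with a significance level of 0.05"; share without significant cancer 0.6; "The proportion of discordant pairs is estimated at 0.2".

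**Step 1. The plan's own figure.** Subjects without significant cancer: 280 × 0.6 = 168. A discordance of 0.2 with a difference of 0.1 gives cells of 0.15 (mp-MRI positive, VERDICT read negative) and 0.05 (the reverse). An exact two-sided McNemar test with n = 168 has 80.06 % power, and 168/0.6 = 280. The stated sample size is reproduced and does not depend on the rule at issue.

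**Step 2. What relabelling does.** On these inputs, among 168 true negatives:
- mp-MRI false positives: 0.4 × 168 = 67.2
- downgraded by VERDICT: 0.15 × 168 = 25.2
- upgraded by VERDICT: 0.05 × 168 = 8.4
- net gain: 25.2 − 8.4 = 16.8, and 16.8/168 = 0.100

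Let m benign mp-MRI-positive lesions be relabelled positive, with a share s of them downgraded by VERDICT. Then

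apparent gain = (16.8 − m·s) / (168 − m).

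**Step 3. Break-even.** The gain stays at 0.100 when 16.8 − m·s = 0.1 × (168 − m), that is, when s = 0.10 for any m. Above 10 % the gain is diluted; below it, the gain rises slightly.

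**Step 4. Illustration.** The documents do not give m or s. For s, take the planning share among mp-MRI false positives, 0.15/0.40 = 37.5 %. Power is asymptotic, Φ[(d√n − 1.96√p)/√(p − d²)], where d is the gain, n = 168 − m, and p = (33.6 − m·s)/n is the discordance. This formula starts at 0.83 rather than the exact 0.80.

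| m (assumed) | s | apparent gain | power |
|---|---|---|---|
| 0 | – | 0.100 | 0.83 |
| 3 | 37.5 % | 15.675/165 = 0.095 | 0.79 |
| 8 | 37.5 % | 13.8/160 = 0.086 | 0.71 |
| 17 | 37.5 % | 10.425/151 = 0.069 | 0.52 |
| 8 | 0 % | 16.8/160 = 0.105 | 0.83 |
| 8 | 100 % | 8.8/160 = 0.055 | 0.41 |

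**Step 5. Sensitivity, if reported.** Here the relabelled lesions join the positives. With 280 − 168 = 112 men with cancer, m = 8 and s = 37.5 %, VERDICT would be charged 3 extra misses among 120, or 2.5 points.

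All counts treat one subject as one lesion, as the sample size calculation does.

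**The case against.** Several points on the other side stand.

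- **Progression is stricter than one positive scan.** The 60-70 % figure is for a positive mp-MRI. The rule asks for change over 6 months to 1 year, and a persisting Likert 3 is excluded. The predictive value of progression is not given and may well be higher. A reader might infer that 30-40 % of these lesions are falsely labelled; the documents do not support that.
- **Later biopsies are probably covered.** A reader might infer that histology obtained after the repeat scan cannot overturn the label, because the biopsy exception is written only for stable Likert 3 lesions. However, the sentence that lets histology supersede mp-MRI has no time limit, and the follow-up branch applies only where no tissue is taken. At most the wording is ambiguous.
- **Unbiopsied 4-5 lesions that stay stable or fall to 3** have no class in the text. One might infer that they have no status at all. The flow chart in Fig. 3 is not available here and may place them, so no omission can be claimed.
- **The direction is mostly conservative.** Above the 10 % break-even the rule hides VERDICT's benefit rather than inventing one.
- **The composite standard is disclosed.** The Discussion names it as a limitation and concedes that the number of biopsies is uncertain. Its ethical defence, however, concerns men with no evident tumour. It does not address lesions that are visible and progressing.
- **Dropping progression-only positives has its own cost.** It would restrict positives to sampled men and bring in verification bias.

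None of this removes the central point: a label for significant cancer is assigned by the comparator without tissue.

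**Conclusion.** The concern holds as a limited but real weakness in a rule that the document fixes. The comparator's repeat reading certifies significant cancer after the same paragraph has found its positive reading insufficient, and imaging progression cannot grade the lesion.

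A reader might go further and say that correct VERDICT downgrades count as misses. In the stated specificity comparison they do not: the lesion leaves the denominator, and VERDICT only loses credit. They become misses only in a sensitivity analysis.

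The size cannot be determined from the documents. The illustrations rest on assumed counts, on the planning share of 37.5 % carrying over to progressing lesions, and on one lesion per subject. With an exact power of 80.06 % there is little reserve, so even a handful of relabelled lesions would matter if VERDICT downgrades a fair share of them. If it downgrades fewer than about 10 %, the bias is small and in VERDICT's favour.

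**What to change.** Keep the primary rule and add three things.

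1. State explicitly that histology obtained at any time up to the analysis cut-off supersedes any follow-up imaging label, for progressive lesions as well as stable ones.
2. Report the primary specificity comparison twice, with progression-only lesions counted as reference-positive and as reference-negative, and give their number.
3. Report the comparison in histology-verified lesions alone. Tissue is sought mainly in mp-MRI-positive lesions, so mp-MRI specificity in this subset will be close to zero by construction. The result should be read mainly as the share of non-significant lesions that VERDICT downgraded.

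The cost is a sentence in the reference standard, a little more analysis of data already collected, and a range around the headline result. Who is biopsied does not change.

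### Excluding stable, unbiopsied Likert 3 lesions removes only mp-MRI positives, which raises apparent mp-MRI specificity; the 10% headcount allowance does not address this, and the effect on power depends on planning values whose population is not stated

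*Protocol article*

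**What the plan says.** In the protocol article, the section VERDICT MRI: histology/mpMRI based reference standard sets three rules that matter here.

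- When mp-MRI is negative (Likert 1-2), mp-MRI is itself the reference.
- When mp-MRI is positive (Likert 3-5), histology takes over if obtained. Otherwise a repeat mp-MRI at 6 months to 1 year decides.
- For one outcome of that repeat scan, "Lesions that remain stable with Likert score 3/5 will be deemed indeterminate and excluded from analysis unless biopsied". Total exclusions are predicted at about 10% of patients.

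The VERDICT MRI section under Data analysis and outcome assessment compares specificity with and without VERDICT, lesion by lesion, with Likert 3 as the positive threshold.

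The Sample size calculation states: "A sample size of 280 subjects achieves 80 % power to detect a difference of 0.1" between "two diagnostic tests whose specificities are 0.7 and 0.6". It adds: "This calculation uses a two-sided McNemar test with a significance level of 0.05". "The prevalence of patients with no cancer or insignificant cancer" is put at 0.6, and "The proportion of discordant pairs is estimated at 0.2". It then allows for 10% of "patients being excluded from the reference standard, a total of 365 patients", of whom 315 form the main study.

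The earlier VERDICT MRI section, under Our proposed new pathway, says the technique is hoped to improve specificity and to "reduce the number of indeterminate examination results".

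**The concern.** Exclusion depends on the result of the comparator test. A lesion can leave by this rule only if mp-MRI called it positive. A patient whom mp-MRI called negative cannot leave by it and is counted as a true negative, so in that group VERDICT can only lose specificity. In the group that is removed, any truly negative lesion is an mp-MRI false positive, which is where VERDICT could gain. The equivocal category is also the one that VERDICT is meant to help with.

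Two things are at stake. The specificity of mp-MRI, the baseline of the primary comparison, is overstated as soon as some excluded lesions are truly negative. The estimated gain, and the power to detect it, may also differ from the plan, because adding 10% to the headcount replaces lost patients but not a selectively lost type of patient.

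**Working it through.** **Inputs.** From the Sample size calculation: specificities 0.6 and 0.7, discordance 0.2, prevalence of negatives 0.6, 280 evaluable, 315 in the main study, 10% excluded, two-sided McNemar test at 0.05. Two inputs are not in the protocol and are varied: *s*, the share of excluded patients who are truly negative, and *r*, the share of those whom VERDICT would have correctly downgraded.

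**1. The plan's own figure.** Negatives: 0.6 × 280 = 168. The discordant cells solve b + c = 0.2 and b − c = 0.1, so b = 0.15 and c = 0.05. Power of the exact test is the sum over m of P(m discordant pairs of n) × P(reject given m), where the gains among m pairs are binomial with probability 0.15/0.20 = 0.75. At n = 168 this gives 80.06%, and at 167 it gives 79.8%. The stated 280 reproduces. The headcount also works: 280/0.9 = 311.1, and 315 × 0.9 = 283.5.

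**2. The same rates applied to all 315 patients.**
- Negatives: 0.6 × 315 = 189
- mp-MRI true negatives: 0.6 × 189 = 113.4
- mp-MRI false positives: 0.4 × 189 = 75.6
- VERDICT gains: 0.15 × 189 = 28.35, which is 37.5% of the false positives
- VERDICT losses: 0.05 × 189 = 9.45, all among mp-MRI true negatives

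**3. Apply the exclusion.** Assume that all 0.1 × 315 = 31.5 exclusions come from this rule. Then:
- negatives left: n = 189 − 31.5s
- apparent mp-MRI specificity = 113.4/n
- gain = (28.35 − 31.5·s·r − 9.45)/n
- discordance = (28.35 − 31.5·s·r + 9.45)/n

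Example with s = 1 and r = 0.375: n = 157.5; specificity 113.4/157.5 = 0.720; gain (28.35 − 11.81 − 9.45)/157.5 = 0.045; discordance 0.165. Of the 75.6 false positives, 75.6 − 31.5 = 44.1 remain.

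| s | mp-MRI specificity | gain, r = 0.375 | power, r = 0.375 | power, r = 0.1875 | power, r = 0 |
|---|---|---|---|---|---|
| 20% | 0.621 | 0.091 | 76% | 81% | 85% |
| 30% | 0.632 | 0.085 | 71% | 79% | 85% |
| 50% | 0.655 | 0.075 | 57% | 73% | 85% |
| 60% | 0.667 | 0.069 | 50% | 71% | 85% |
| 100% | 0.720 | 0.045 | 22% | 57% | 85% |

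Power is for the exact McNemar test, with n rounded to a whole number.

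**4. Direction of the effect on the gain.** The gain falls below 0.10 when 18.9 − 31.5·s·r < 0.10 × (189 − 31.5s), that is, when r > 0.10. If VERDICT would correct fewer than 10% of the excluded false positives, the exclusion overstates the gain instead. The rise in mp-MRI specificity does not depend on r.

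**5. The other reading.** If the planning rates already describe evaluable patients, there are 0.9 × 189 = 170.1 negatives with cells 0.15 and 0.05, and power is about 81%.

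**The case against.** The strongest reply is that the planning rates are attached to the 280 analysed subjects and the 10% is added afterwards, so they describe evaluable patients and power is as stated. The text allows this reading but does not settle it. A consistency check gives limited help. With specificity 0.6, prevalence 0.6 and the quoted negative predictive value of 90-95%, the full-cohort reading implies a positive predictive value of 0.36/0.60 = 60% to 0.381/0.621 = 61%, within the 60-70% that the protocol reports. The evaluable reading, after adding back 10% excluded positives of whom 50-100% are benign, gives about 51-60%. At a lower benign share both readings fit, so this supports the full-cohort reading without proving it.

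Three stronger readings are tempting and are not supported.

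- **That the excluded lesions are mostly false positives.** This is plausible for unbiopsied, equivocal lesions that did not progress, but the protocol calls them indeterminate and gives no share. The 60-70% predictive value covers Likert 3-5 together.
- **That VERDICT loses its room to improve.** At worst 44 of 76 false positives remain.
- **That power is well under 80%.** This needs full-cohort rates and a substantial correction rate among excluded lesions.

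Other limits stand. The 10% is a total and may include other reasons for exclusion. The analysis is by lesion and the calculation by patient, so the figures are approximate. An analysis plan that is not shown may already hold sensitivity analyses. None of this changes the fact that the rule, as the protocol fixes it, selects on the comparator's result.

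**Conclusion.** The point holds in a limited form. The exclusion depends on the mp-MRI result and raises apparent mp-MRI specificity whenever some removed lesions are truly negative: from 0.60 to 0.62 at a 20% benign share and to 0.72 at 100%, if all 10% are lost through this rule and the planning rates are full-cohort values. The sample size arithmetic is correct, but it handles the loss as headcount only and does not name the population behind its rates.

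The power effect is conditional. It runs from 76% down to 22% (benign share 20% to 100%) with full-cohort rates and equal VERDICT correction, and from 81% to 57% at half that correction rate. Power is about 81% if the rates describe evaluable patients, and about 85% if VERDICT corrects none of the excluded lesions. The 22% is a worst case within these assumptions, not an expected value.

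A reader might also infer that unbiopsied Likert 4-5 lesions that stay stable have no reference class. The text gives none, but the derivation flow chart (Fig. 3) is not shown and may do so.

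**What to change.** **Analysis.** Pre-specify two further versions of the primary comparison that keep stable, unbiopsied Likert 3 lesions: once all as reference-negative, once all as reference-positive. Report them beside the exclusion analysis and base the conclusion on whether the gain holds across them. For specificity, the all-positive version equals the exclusion result, since specificity uses reference-negatives only. Its information lies in sensitivity, where each lesion that VERDICT downgrades then counts as a loss, so sensitivity should be reported with it. The two versions are reference cases, not strict limits, because truth may differ between lesions that VERDICT did and did not downgrade.

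**Planning values.** State whether 0.6, 0.7, the 0.6 prevalence and the 0.2 discordance describe all patients or those left after exclusion. If all patients, restate specificities, discordance and power for the post-exclusion set.

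**What not to do.** Do not make every non-progressing lesion, including stable Likert 4-5, reference-negative in the primary analysis. Stable cancers that VERDICT downgrades would then count as gains. With 60% of the 31.5 truly negative and the same 37.5% downgrade rate, 12.6 cancers enter as negatives and the apparent gain is (28.35 + 4.725 − 9.45)/201.6 = 11.7 points against a true 10.

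**Cost.** A few extra analysis runs, some wording, and possibly a less favourable stated power. Patient care does not change.
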